**3.4 Drug Intervention**

Group K: 0.3 mg/kg esketamine administered before skin incision.

Group C: Equivalent dose of saline administered before skin incision.

**4. Study Subjects**

**4.1** **Inclusion Criteria:**

ASA classification I-III.

Age ≥18 years, weight 50-100 kg, gender not restricted.

Scheduled for elective cholecystectomy under general anesthesia.

Willing to sign informed consent.

**4. 2 Exclusion Criteria**

Known allergy to esketamine hydrochloride or its excipients.

Severe cardiovascular, respiratory, hematologic, endocrine, or hepatic/renal dysfunction.

Risk of elevated blood pressure, intraocular pressure (e.g., glaucoma), or intracranial pressure.

Neurological or psychiatric disorders.

Alcohol abuse or long-term use of sedatives or analgesics.

Surgery or use of study drugs within one week before the trial.

Participation in other drug clinical trials within the last three months.

Communication barriers (e.g., reading/writing difficulties, language barrier, visual/hearing impairment) hindering study completion.

Refusal to sign informed consent.

4.3 Withdrawal Criteria

Occurrence of serious adverse events.

Protocol violations (e.g., unexpected ICU transfer, poor patient compliance).

Patient request to withdraw.

Loss to follow-up with no efficacy data collected.

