**1. Background**

Laparoscopic cholecystectomy is widely used in clinical practice due to its minimal trauma and rapid postoperative recovery. The gallbladder and biliary tract are areas densely innervated by the vagus nerve. During surgery, stimulation, traction, and dissection of the gallbladder or exploration of the common bile duct can cause biliary-cardiac reflex, leading to reflex coronary artery spasm, myocardial ischemia, cardiac function suppression, bradycardia, arrhythmia, and in severe cases, cardiac arrest. Previous literature reports that the incidence of circulatory arrest during biliary surgery is 3.07 times that of non-biliary surgery, with an occurrence rate of biliary-cardiac reflex ranging from 30% to 75%. Therefore, exploring an appropriate anesthesia management strategy to prevent biliary-cardiac reflex is crucial for the prognosis of patients undergoing laparoscopic cholecystectomy. Administering a low dose of esketamine after anesthesia induction, utilizing its sympathetic stimulation effect to raise blood pressure, increase heart rate, and suppress adverse reflexes, may help counteract vagal reflexes during cholecystectomy. Esketamine is the right-handed isomer of ketamine, exhibiting similar pharmacological characteristics by blocking NMDA receptors for analgesic effects. It has twice the affinity for NMDA receptors as racemic ketamine, with no difference in onset and duration of action but higher bioavailability and shorter half-life. In the nervous system, NMDA receptors are involved in pain signal transmission and amplification. Inflammatory factors released from tissue injury or stimulation increase NMDA receptor activity, leading to pain signal transmission and amplification. Hence, inhibiting NMDA receptor activity can alleviate pain perception. Therefore, we investigated the effect of low-dose esketamine on biliary-cardiac reflex during cholecystectomy and postoperative pain.

- 1. **Primary Objective**

To observe the effect of administering low-dose esketamine after anesthesia induction on biliary-cardiac reflex and postoperative pain during cholecystectomy.

- 1. **Secondary Objectives**

1. The incidence of adverse reactions to perioperative use of esketamine.
2. The effects of perioperative esketamine use on postoperative depression, anxiety, and cognitive function in patients.

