**3.3 Randomization and Blinding**

Patients will be randomized into two groups: control group C and experimental group K using the Research Randomizer website. The results will be stored in opaque envelopes, managed by a researcher not involved in patient recruitment, data collection, perioperative management, or postoperative follow-up. Before surgery, the coordinator will prepare the drugs according to the randomization results and provide them to the anesthesiologist responsible, labeled as "research drug" with the patient's random number. The anesthesiologists, surgeons, nurses, and follow-up personnel involved in the trial will be blinded to the group assignments until the end of the trial when all data have been recorded and analyzed.

**Emergency Unblinding:** In case of emergencies requiring knowledge of the treatment received, the principal investigator can decide to open the envelope to reveal the group assignment. Once opened, the case will be considered a dropout, and the reason recorded. The patient will not be included in efficacy analysis but will be included in adverse reaction analysis. If more than 20% of the envelopes are opened, the double-blind trial will be invalidated.

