**5.2 Follow-up Plan**

Screening Period: 0-7 days before surgery, screen according to inclusion/exclusion criteria. Provide informed consent and complete the following assessments:

1. Basic information: name (initials), age, height, weight, medical history, preoperative diagnosis, ASA classification, comorbidities, marital status.
2. Preoperative depression/anxiety (HAD scale) and cognitive function (MMSE), pain assessment (VAS).
3. Laboratory tests: blood routine, biochemistry, urine routine, coagulation function within one week before consent.
4. Other auxiliary examinations: ECG, cardiac function.
5. All medications used within three days before surgery.

**5.2.** Follow-up Period

Evaluation Items Include:

Vital Signs upon Room Entry: Record the patient's vital signs upon entry into the operating room.

Surgery and Anesthesia Records: Record blood pressure, heart rate, oxygen saturation (SpO2), surgical duration, blood loss, fluid infusion, urine output before and after drug administration, anesthesia duration, and incidence of biliary-cardiac reflex.

Intraoperative Unexpected Events: Record any decrease in oxygen saturation (<90%), hypotension, hypertension, bradycardia, tachycardia, laryngospasm, intraoperative awareness, post-extubation nausea and vomiting, salivation, increased secretions, dizziness, restlessness, agitation, cognitive impairment, disorientation, respiratory depression, diplopia, blurred vision, hallucinations, and nightmares.

Postoperative Pain Assessment: Evaluate the intensity of postoperative pain at 24, 48, and 72 hours using the Visual Analog Scale (VAS) in both resting and movement states (e.g., coughing or deep breathing).

Usage of Postoperative Rescue Analgesics: Record the time of the first request for rescue analgesics and the total amount of rescue analgesics used within 72 hours.

Postoperative Depression/Anxiety and Cognitive Function: Assess using the Hospital Anxiety and Depression Scale (HAD) and the Mini-Mental State Examination (MMSE) at postoperative follow-ups.

Adverse Reactions: Record all adverse reactions within 72 hours postoperatively, including dizziness, nausea, vomiting, subjective reports of dreams, skin itching, hallucinations, diplopia, postoperative delirium, agitation, and other mental-related side effects.

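### Section 4.3 withdraws patients for serious adverse events and ICU transfer although treatment is one pre-incision dose, so follow-up can end because of outcome

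*Protocol*

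**What the plan says.** Section 4.3 of the protocol lists four withdrawal criteria. The first is "Occurrence of serious adverse events". The second is "Protocol violations (e.g., unexpected ICU transfer, poor patient compliance"), which places an ICU transfer among protocol violations. The third is the patient's own request. The fourth, "Loss to follow-up with no efficacy data collected", suggests that the list is about leaving the study and not about stopping a drug. The section does not say what withdrawal does to later data collection or to any analysis.

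Three other places bear on this:

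- **Treatment (section 3.4):** "Group K: 0.3 mg/kg esketamine administered before skin incision", with saline at the same time point in the control group. No later study dose is described.
- **Safety:** a secondary objective is "The incidence of adverse reactions to perioperative use of esketamine", and section 5.2 instructs staff to "Record all adverse reactions within 72 hours postoperatively".
- **Dropouts (section 3.3):** the only rule on how a dropout is analysed applies to emergency unblinding: "The patient will not be included in efficacy analysis but will be included in adverse reaction analysis".

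**The concern.** Once the single dose has been given there is no study treatment left to stop. Withdrawal for a serious adverse event or an ICU transfer can then only end study follow-up, end the use of the patient's data, or both. An ICU transfer is something that happens to the patient. It is not a departure from the protocol by patient or staff.

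Both grounds arise after randomisation and can follow from the outcome under study. The Background describes the reflex as leading to "bradycardia, arrhythmia, and in severe cases, cardiac arrest", so the most severe reflex cases can meet the withdrawal criterion because they had the primary event.

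Two things are at stake. First, later measurements would be missing in a way that depends on outcome. This includes pain, which is part of the primary objective and is measured at 24, 48 and 72 h. Second, if withdrawn patients were also left out of the efficacy analysis, the reflex comparison would no longer be between the groups as randomised.

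**Working it through.** **1. What would be lost if follow-up ends at withdrawal.** Take a dosed patient with a serious event during surgery or soon after, and set section 4.3 against section 5.2.

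| Record in section 5.2 | When collected | Effect of withdrawal on the day of surgery |
|---|---|---|
| Reflex | During surgery | Normally already recorded |
| The triggering event | When it occurs | Normally already recorded |
| VAS at rest and on movement | 24, 48, 72 h | Not collected |
| Rescue analgesic use | To 72 h | Incomplete |
| HAD and MMSE | Postoperative follow-ups (no times given) | Not collected |
| Adverse reactions | To 72 h | Later reactions not observed |

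The firm loss is therefore in the postoperative records. The reflex result is lost only if withdrawn patients are also excluded from the analysis.

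**2. The plan's own figure.** Section 3.2 gives a control rate of 40%, a 25% reduction, two-sided α = 0.05 and β = 10%. Read as 25 percentage points (40% vs 15%), with unpooled variance:

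n per arm = (1.960 + 1.282)² × (0.40 × 0.60 + 0.15 × 0.85) / 0.25² = 61.8, rounded up to 62, or 124 in total.

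This reproduces the stated 124. Recruitment is 148, or 74 per arm. The point does not depend on this figure; it only supplies the rates for step 3.

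**3. Illustration if withdrawn reflex cases were also excluded from efficacy.** The documents give no withdrawal rate, so the share w of reflex cases removed is an assumption. For a true rate p, the observed rate is p(1 − w)/(1 − pw).

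*Same w in both arms, true rates 40% vs 15%:*

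| w | Control | Esketamine | Difference (points) | Power |
|---|---|---|---|---|
| 0 | 40.0% | 15.0% | 25.0 | 93.4% |
| 10% | 0.360/0.960 = 37.5% | 0.135/0.985 = 13.7% | 23.8 | 91.4% |
| 20% | 0.320/0.920 = 34.8% | 0.120/0.970 = 12.4% | 22.4 | 88.6% |
| 30% | 0.280/0.880 = 31.8% | 0.105/0.955 = 11.0% | 20.8 | 85.0% |

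Power starts from 74 per arm less the cases removed and uses the pooled-variance normal test. On that test, 62 per arm gives 88.6%, so these values are not on quite the same scale as the plan's 90%. Equal removal shrinks the absolute difference. It multiplies the odds in each arm by (1 − w), so the odds ratio does not change.

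*Removal in the esketamine arm only, no true effect (40% vs 40%):*

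- w = 10%: 40.0 − 37.5 = 2.5 points of false benefit
- w = 20%: 40.0 − 34.8 = 5.2 points
- w = 30%: 40.0 − 31.8 = 8.2 points

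**4. What these shares mean in patients.** In the control arm, 10-30% of reflex cases is 74 × 0.40 × 0.10 = 3.0 to 74 × 0.40 × 0.30 = 8.9 patients, or 4-12% of the arm. That many serious events or ICU transfers may be high for an elective population from which section 4.2 excludes severe cardiovascular and respiratory dysfunction.

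**The case against.** The strongest reply is that section 4.3 only lists criteria. It does not say that data are deleted or that anyone leaves an analysis. Analysis sets commonly belong in the statistical analysis plan, which may exist, and their absence here is no fault. This stands. A reader might infer that the rule removes severe reflex cases from the primary comparison, but the protocol does not say so. It would follow only if the section 3.3 handling of unblinded patients were extended to withdrawals.

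A reader might also infer that serious events drop out of the safety results. The text does not support that. The triggering event would normally be recorded, section 5.2 makes no exception for withdrawn patients, and the nearest dropout rule keeps cases in the adverse-reaction analysis.

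Nor can the 20% dropout allowance be read as a forecast of such exclusions. The plan's margin is 148 − 124 = 24 patients, for dropout in general, with no breakdown by reason.

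Two smaller replies also stand. An event between randomisation and dosing can be a working reason for withdrawal, so the point applies to dosed patients. Poor compliance has no evident link to a reflex under general anaesthesia and is the weakest of the grounds.

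What the reply does not answer is data collection. A statistical analysis plan can define analysis sets, but it cannot recover 24, 48 and 72 h measurements that were not taken because the protocol ended participation.

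**Conclusion.** The point holds as a fault in a stated rule. For dosed patients, section 4.3 ends participation on outcome-related grounds, misclassifies ICU transfer as a protocol violation, and is in tension with the 72 h recording in section 5.2 and with the safety objective. The direct consequence is outcome-dependent loss of postoperative pain, HAD, MMSE and later adverse-reaction data.

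Any effect on the reflex comparison is conditional on withdrawn patients also being excluded from efficacy. Under that condition and the assumed 10-30% removal, the absolute difference falls from 25 points to between 23.8 and 20.8 if both arms are affected alike. That works against esketamine on the absolute scale. A false benefit, of 2.5-8.2 points, arises in the illustration only if removal is confined to the esketamine arm. Actual numbers are unknown and may be small. This is an inexpensive correction worth making, not a defect that invalidates the design.

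**What to change.** Reword section 4.3 so that, for patients who have received study drug:

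- serious adverse events, ICU transfers and protocol deviations are recorded as events, and an ICU transfer is no longer called a protocol violation;
- data collection continues to 72 h as in section 5.2;
- the patient stays in the reflex and safety analyses by allocated group unless consent for data use is withdrawn.

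Reconcile sections 3.3, 4.3 and 5.2, so that it is clear whether a dropout, a withdrawal and an unblinded case are handled alike, and what is still collected in each. A serious event could plausibly prompt emergency unblinding as well as withdrawal, so the same patient may fall under both rules.

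The change concerns data only; clinical care of these patients is unchanged. The cost is a wording amendment and 72 h data on a few patients. It should be made before the rule is applied, because measurements not taken cannot be recovered.

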5.1 Study Flow

Obtain written informed consent from patients before surgery, screen according to inclusion/exclusion criteria, and randomize using the randomization website. Store the randomization numbers in opaque envelopes. Preoperatively, introduce patients to the use of the Visual Analog Scale (VAS) for pain, the Hospital Anxiety and Depression Scale (HAD), and the Mini-Mental State Examination (MMSE).

All patients will undergo general anesthesia with intubation using a video laryngoscope, and be monitored using a Chinese multifunctional monitor for invasive arterial pressure, heart rate, SpO2, temperature, and end-tidal CO2. Anesthesia will be induced with propofol (2-3 mg/kg), rocuronium (0.6-1 mg/kg), and sufentanil (0.25-0.5 µg/kg). After loss of consciousness (absence of corneal and eyelid reflexes), tracheal intubation will be performed. Anesthesia will be maintained with remifentanil (0.1-0.3 µg/kg/min), propofol (3-4 mg/kg/h), and sevoflurane (0.7-1.0 MAC), with dosage adjusted by the anesthesiologist.

Definition of Biliary-Cardiac Reflex: During gallbladder manipulation or traction, if heart rate decreases (HR < 60 bpm) or drops by ≥20% from baseline along with a ≥20% drop in blood pressure from baseline, it will be classified as a biliary-cardiac reflex. If reflex occurs, surgery will be paused, and 0.5 mg of atropine will be administered intravenously. If recovery is not achieved quickly, the operation will be stopped, and rescue medications such as ephedrine, isoproterenol, or epinephrine will be administered.

Surgery will be performed by the same team of surgeons. Sevoflurane will be stopped 30 minutes before the expected end of surgery, and propofol and remifentanil infusions will be stopped at the end of the surgery. Patients will be observed for half an hour in the operating room after waking and restoration of spontaneous breathing before being transferred to the ward.

Postoperative Rescue Analgesia: Sufentanil will be titrated for analgesia. If VAS score > 3 (moderate to severe pain) or upon patient request, rescue analgesia will be administered and recorded. If VAS score ≤ 3 or if there is no request, no additional analgesia will be provided.

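### The two sentences of the rescue-analgesia rule contradict each other; the *or* in the second should be *and*

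*Protocol*

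**What the plan says.** The rule is in Protocol section 5.1, in the paragraph on postoperative rescue analgesia. After stating that sufentanil is titrated, it gives two instructions in succession:

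- To give: "If VAS score > 3 (moderate to severe pain) or upon patient request, rescue analgesia will be administered and recorded".
- To withhold: "If VAS score ≤ 3 or if there is no request, no additional analgesia will be provided".

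Two sets of measurements in section 5.2 (Follow-up Period) are linked to this rule. For rescue use, staff are to "Record the time of the first request for rescue analgesics and the total amount of rescue analgesics used within 72 hours". Pain is scored by VAS at 24, 48 and 72 hours, at rest and on movement. Pain also belongs to the primary objective, which is "To observe the effect of administering low-dose esketamine after anesthesia induction on biliary-cardiac reflex and postoperative pain during cholecystectomy".

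**The concern.** A sentence that says when to withhold should cover exactly the cases that the sentence on giving leaves out. Here it covers more. The first sentence makes either trigger sufficient. The second, read literally, makes both necessary, because the absence of either one is enough to withhold. The cases with only one trigger present, which a two-trigger rule exists to settle, are therefore told both to receive and not to receive rescue.

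Two things are at stake. The first is care: the text permits a reading in which a patient above 3 who stays silent goes untreated. The second is measurement: the 72-hour rescue total depends directly on who is treated, and rescue can change the VAS scores. If some staff follow the first sentence and others the second, that variation has nothing to do with esketamine.

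**Working it through.** The question is one of logic, and the protocol gives no figure to reproduce.

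**Inputs (section 5.1).** Let A be VAS > 3 and B be a request by the patient, both judged at the same moment.

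- First sentence: give if A or B.
- Second sentence: withhold if (not A) or (not B).

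**What the complement should be.** By De Morgan's rule, not (A or B) = (not A) and (not B). The second sentence has *or* where the complement needs *and*.

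**All four combinations.**

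| VAS | Request | First sentence | Second sentence as written | Second sentence with *and* |
|---|---|---|---|---|
| > 3 | yes | give | silent | silent |
| > 3 | no | give | **withhold** | silent |
| ≤ 3 | yes | give | **withhold** | silent |
| ≤ 3 | no | silent | withhold | withhold |

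As written, 2 of 4 combinations conflict (rows two and three). With *and*, 0 of 4 conflict and none is left without an instruction: three give, one withholds.

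**The other one-word repair.** Changing *or* to *and* in the first sentence instead also yields 0 of 4 conflicts, with one combination giving and three withholding. But it would deny rescue to a patient above 3 who does not ask, and to one at 3 or below who does. That discards the protocol's explicit instruction to treat on either trigger, so the second sentence is the one to correct.

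**Rest and movement scores.** Section 5.2 takes both readings, and section 5.1 does not say which one triggers rescue. Crossing rest, movement and request gives 2 × 2 × 2 = 8 combinations. Whichever reading is used, the other simply doubles each row of the table: 2 × 2 = 4 of 8 conflict as written, and 2 × 0 = 0 of 8 after the change. If neither reading is singled out, 2 of 8 stay undetermined after the change, namely those with one reading above 3, the other not, and no request. The correction thus removes the contradiction for any given VAS reading and does no more than that.

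These are counts of logical combinations, not of patients or probabilities.

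**The case against.** The strongest reply is that the sentences may be meant in sequence. The paragraph opens with titration, and the second sentence speaks of *additional* analgesia. On that view the first sentence starts rescue and the second stops it: no further dose once the score is 3 or below or nothing more is asked for. Decisions about the first dose would then follow the first sentence alone and would not conflict. The wording lends this modest support, but it does not clear the text. A patient still above 3 after a dose who does not ask again would remain ambiguous, and the protocol nowhere sets out such a sequence.

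A second reply is that the intent is plain and staff will follow the first sentence. Many may, and that limits the weight of the point. It does not make the second sentence correct, and it is a separate instruction that can be followed as it stands.

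A third is that the effect is unquantified. That is true. The conflict bites only when a VAS score is known, and postoperative scores are scheduled only at 24, 48 and 72 hours. The protocol does not say whether pain is also scored when a patient asks for relief, so neither conflicting case can be given a frequency. Nor is there reason to expect bias between arms: "The anesthesiologists, surgeons, nurses, and follow-up personnel involved in the trial will be blinded to the group assignments". The biliary-cardiac reflex, the only outcome used for the sample size in section 3.2, does not depend on this rule.

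**Conclusion.** The contradiction is real: 2 of 4 VAS and request combinations receive opposite instructions, and no other part of the protocol sets precedence. This rests on reading the two sentences as applying at the same moment; the sequential reading narrows the conflict without removing it. That *or* was written for *and* is the likeliest explanation, inferred from the first sentence and not stated. The consequence is a literal reading that leaves moderate to severe pain untreated, and possible noise of unknown size in the rescue total and the VAS scores. It is a minor wording error in an operative treatment rule, and worth correcting for that reason.

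**What to change.** In the second sentence of the rescue rule in section 5.1, replace *or* with *and*, so that analgesia is withheld only when VAS is ≤ 3 **and** the patient has not asked. Leave the first sentence as it is.

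The cost is one word. Sample size, drugs, visit schedule and record form do not change.
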